#### Sample size

We plan to conduct a study with a sample exploratory nature because the specific intervention has not yet revealed data in IOH in the literature. In the pilot phase, 30 participants each will be investigated in two groups. Then, the results of the primary outcome are used for sample size estimation. If the pilot can be continued, we will use it as an interim analysis in our study.

#### Recruitment

The primary site of recruitment is the Education Center of the Faculty of Dentistry (Semmelweis University, Budapest, Hungary), which receives on average 10,179 patients per month. The trial will be advertised on posters and social media.

#### Assignment of ﻿interventions

##### Allocation & blinding

Eligible patients will be randomly allocated to the intervention and control groups by REDCap. Randomization sequences will be generated by using the big stick design [34]. Trial participants and outcome assessors will be blinded. In addition, the data analyst will have access to the anonymized datasheet, without being aware of the allocated intervention. Dark, uniformly packaged, sealed bottles of mouthwash labeled A and B will contain the assigned interventions, which will be given to patients after the randomization. A dental hygienist, who will not be involved in the assessments of the outcomes, will hand out the boxes with the assigned mouthwashes to the participants and supervise the rinsing process. The examiner will examine the patients in a separate room from rinsing without knowing their assigned intervention. The information in an opaque envelope about which mouthwashes are A and B will be kept in the safe of the guarantor of the trial.

##### Statistical methods

We will report on baseline characteristics and differences between the two arms. For continuous primary and secondary endpoints, we will report the mean results of the groups and changes at the different time points. Due to the non-inferiority study design, we choose the non-inferiority limit (*d* = 1) as the most considerable clinically acceptable difference. For the side-effect questionnaire, we will create a summary table showing the frequency of adverse events and all patient comments. In the case of any missing data, sensitivity analyses will be conducted to determine the most suitable approach.

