### Eligibility criteria

#### Inclusion criteria

►Aged 18 or older►Organoleptic test score (OLS) ≥ 2 for IOH (A trained dentist will perform the measurements.)►Patients with at least 20 teeth.►Eight hours of use of scented oral hygiene product, 4 h of eating, and 2 h of drinking restriction►Restriction of alcohol, caffeine, perfume usage, and food intake with characteristic smell on the day of investigation

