### Outcomes

#### Primary outcome

The primary endpoint of the study will be the changes in organoleptic test scores as measured by a trained dentist with the gold standard 6-point (0–5) intensity scale [32].

Tests will be performed three times (Table 1): at baseline, immediately after and 3 h after rinsing with mouthwash. Two changes will be measured between the following time points: 1) baseline - immediately after rinsing, and 2) baseline - 3 h later; as suggested by Yaegaki et al. in their halitosis research [33].

**Table 1 Tab1:** Participant timeline.

			Study period			
	Enrollment	Allocation	Post allocation			Close-out
Time point	Starting from January 18, 2024	Baseline	Intervention	Immediately after mouthwash use	3 h later	December 1, 2025
Enrollment:						
Eligibility screen	X					
Informed consent		X				
Randomization		X				
Interventions:						
Hyperpure chlorine dioxide			X			
Chlorhexidine			X			
Assessments:						
Organoleptic score	X	X		X	X	
Volatile sulfur compound measurement with a gas chromatograph		X		X	X	
Self-perceived halitosis		X		X	X	
Subjective experiences, adverse events				X	X	
Statistical analysis						X

Schedule of enrollment, interventions, and assessments.

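### The only analysis stated for the primary endpoint is group means and changes in organoleptic score; adjustment for baseline is neither planned nor excluded, and declaring it would gain precision of uncertain size

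*Protocol article*

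**What the plan says.** The Primary outcome section defines the endpoint as a change: "The primary endpoint of the study will be the changes in organoleptic test scores as measured by a trained dentist", on a scale from 0 to 5. It then specifies two of them: "Two changes will be measured between the following time points: 1) baseline - immediately after rinsing, and 2) baseline - 3 h later". Baseline is measured in every participant: "Tests will be performed three times (Table 1): at baseline, immediately after and 3 h after rinsing with mouthwash".

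Statistical methods gives one sentence on how the continuous endpoints, primary and secondary, are handled: "we will report the mean results of the groups and changes at the different time points". The limit d = 1 follows in the next sentence. The same section says that baseline characteristics and differences between the arms will be reported. It names no estimator, interval or covariate.

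Allocation & blinding gives the randomisation method, "Randomization sequences will be generated by using the big stick design", and mentions no stratification by baseline OLS. Entry requires "Organoleptic test score (OLS) ≥ 2 for IOH" (Inclusion criteria). The Sample size section carries the primary-outcome results of the 30 + 30 pilot participants into a later sample size estimation.

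**The concern.** The endpoint, the limit and the pilot estimate that feeds the sample size are all expressed in terms of change scores, and nothing is said about using baseline OLS as a covariate. On this scale, change is tied to baseline: a participant at 2 can fall by at most 2 points, one at 5 by up to 5. An unadjusted change score carries that variation into the arm difference.

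Two things are at stake. The interval held against d = 1 may be wider than it needs to be. And in any one trial of this size, a chance difference in baseline severity is over-corrected when the slope of the later score on baseline is below 1, so the arm that starts worse looks as if it improved more. The SD passed to the sample-size step would also be larger than an adjusted analysis requires.

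**Working it through.** **Inputs from the article.** 30 per arm; scale 0 to 5; entry at OLS ≥ 2; limit d = 1, read here as one OLS point because no unit is given. There is no figure to reproduce: the Limitations section says that a sample size calculation was not possible.

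**Assumptions (not in the article).** Correlation r of baseline with the later score 0.3 to 0.7; OLS SD 0.8 to 1.2; one-sided 0.025; true difference 0.

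**1. General formula.** Write B for SD_baseline and P for SD_post.
- Change-score variance: B² + P² − 2rBP
- ANCOVA residual variance: P²(1 − r²)
- Difference: B² − 2rBP + r²P² = (B − rP)²

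The saving is never negative. It is zero when the slope rP/B equals 1.

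**2. Equal SDs (B = P).** The variance ratio, ANCOVA to change, is (1 − r²)/[2(1 − r)] = (1 + r)/2.

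| r | Ratio | Saving | Simulated ratio, 30 per arm | 95% half-width at SD 1.0, change → ANCOVA |
|---|---|---|---|---|
| 0.3 | 0.65 | 35% | 0.68 | 0.60 → 0.48 |
| 0.5 | 0.75 | 25% | 0.77 | 0.51 → 0.44 |
| 0.7 | 0.85 | 15% | 0.89 | 0.39 → 0.36 |

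The half-width is 1.96 × SD × √(2/30). The simulation used 4,000 trials per value of r; its slightly higher ratios are in line with the small cost of estimating the slope.

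**3. Unequal SDs.** Selecting on baseline shrinks B but, in a linear model, leaves the slope and the residual variance unchanged. As an illustration (not trial data), take a standard bivariate normal with baseline kept above its mean. The baseline variance becomes 1 − 2/π = 0.363, and the saving is (1 − r)² × 0.363 divided by [(1 − r²) + (1 − r)² × 0.363], with r the correlation before selection.
- r = 0.3: 0.178/1.088 = 16%
- r = 0.5: 0.091/0.841 = 11%
- r = 0.7: 0.033/0.543 = 6%

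With B = 0.7, P = 1.0 and r = 0.7, the saving is (0.7 − 0.7)² = 0. In the other direction, treatment that compresses the later scores towards 0 lowers P and raises the saving.

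**4. Chance imbalance.** With 30 per arm, the 95% limits of the baseline difference are ±1.96 × B × √(2/30): ±0.41 at B = 0.8 and ±0.51 at B = 1.0. A raw change leaves a share (1 − slope) of this in the estimate, with opposite sign. At the 95% limit that is 0.28 to 0.35 points for slope 0.3, 0.20 to 0.25 for 0.5, and 0.12 to 0.15 for 0.7. A narrower baseline spread reduces these in proportion.

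**5. Against d = 1, equal SDs.** At SD 1.0, power with raw change is 90.6%, 97.2% and 99.9% for r = 0.3, 0.5 and 0.7; with ANCOVA it is 98.2%, 99.4% and 100.0%. At SD 1.2 and r = 0.3 it rises from 77.9% to 92.3%.

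**6. Sample-size step.** Planning on the change-score SD instead of the residual SD raises the required number by 1/0.85 − 1 = 18% to 1/0.65 − 1 = 54% with equal SDs. In the illustration of step 3 it is 1/0.94 − 1 = 6% to 1/0.84 − 1 = 19%.

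**The case against.** The strongest reply is that the article does not commit to an unadjusted comparison. The sentence in Statistical methods describes what will be reported. A change endpoint is fully compatible with adjustment: regressing the change on arm and baseline gives the same arm effect and interval as regressing the later score on arm and baseline. The choice of covariates is commonly left to a full protocol or SAP, which is not shown, and silence about stratification says nothing about the model. All of this stands. A reader might infer that an unadjusted primary comparison is planned; the text does not support that.

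A reader might also take the equal-SD formula at face value and conclude that 60 participants with ANCOVA are worth 60/0.65 = 92 with raw change. That needs equal SDs and r = 0.3, and the entry rule makes equal SDs doubtful. Nor can one argue that the entry rule lowers r and so enlarges the gain. In the illustration starting from r = 0.5, the restricted correlation is 0.33, for which the equal-SD formula would give 34%; the true saving is 11%.

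Finally, subtracting baseline does not leave the imbalance untouched. It removes the raw difference and, with a slope below 1, overshoots. Randomisation keeps the estimate unbiased on average. With SD 1.0, power for d = 1 is already above 90%, and a larger planning SD errs on the safe side.

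What survives is that the saving cannot be negative, the data are already collected, and the article states no use of baseline in the comparison.

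**Conclusion.** This is an efficiency improvement worth making. It is not an error or a contradiction in the article. The only stated analysis is group means and changes; adjustment for baseline OLS is left open. An adjusted comparison saves (SD_baseline − r × SD_post)² per participant: 15% to 35% of the change-score variance for r = 0.7 to 0.3 with equal SDs, but possibly only about 5% to 15%, or nil, if the entry rule narrows the baseline spread. The article gives neither r nor an SD, so the size cannot be fixed more closely. The formulas also treat a bounded six-point score as roughly linear and normal.

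A claim that the result would be biased is not supported: both estimators are unbiased on average. What adjustment changes is the width of the interval and how far one trial's chance imbalance moves the estimate.

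**What to change.** Add to Statistical methods that the arm difference in OLS at each post-rinse time is estimated by ANCOVA with arm and the participant's own baseline value. Do the same for the volatile sulfur compounds and the self-perceived halitosis scale. Hold the confidence bound of the adjusted OLS difference against d = 1. In the step described under Sample size, use the ANCOVA residual SD, so that planning and analysis rest on the same estimator. Keep the raw means and changes as description.

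Settle this before the pilot results are seen, because the Sample size section allows the pilot to serve as an interim analysis. The Protocol amendments section already provides the route: the registration and the final article. If an unshown SAP already specifies the adjustment, a statement to that effect is enough.

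The cost is about one degree of freedom and a line of wording, with no new data.

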##### Safety and adverse events

Side effects of chlorine dioxide at this low concentration are not known yet [28]. Prolonged use of CHX-containing mouthwash can lead to several adverse events with a relatively high frequency and it is hypothesized that a specific type of control mouthwash may have fewer undesirable effects [12]. We will ask the patients about their experiences at each time point. If patients experience any adverse events, we will record these follow-up questionnaires. SC will verify the validity of adverse events; the relevant ones will be reported to the National Institute of Pharmacy and Nutrition (OGYÉI). If any safety concerns arise, we will stop the study immediately.

##### Withdrawal from study

Due to the length of the study, we expect a small number of eligible participants to withdraw or drop out. Previous studies [36–38] have reported a dropout rate of 10%.

##### Public and patient involvement

The protocol development phase involved three patients. We asked them to read the patient information leaflet and give informed consent after being introduced to the purpose, primary outcome, and protocol of the study. They thought that the written materials were transparent and informative. Our clinical question was deemed highly relevant by the patients. They said that the one-day caffeine restriction was too long, and that they could not imagine not brushing their teeth the night before the investigation. Thus, we reduced the time limits in the protocol, oral hygiene restriction from 12 to 8 h, and caffeine from one day to the day of the investigation. In addition, they expressed their preference for flavored mouthwashes.

#### Dissemination

##### Protocol amendments

Any potential deviation from the protocol will be discussed with the SC. If the team accepts the changes, they will be reported in the protocol registration and the final article with the data.

##### Publication policy

We plan to publish our results regardless of the results and the feasibility of the more extended version.

## Discussion

This research focuses on comparing the effectiveness of hyperpure ClO_2_ compared to chlorhexidine, as this specific intervention has not been thoroughly investigated in IOH. Currently, there is only one similar article [39] that compares chlorhexidine and ClO_2_. This particular intervention provides an opportunity to conduct a pilot trial. If our hypothesis is confirmed, we expect that hyperpure ClO_2_ is not inferior to chlorhexidine because of the dual action of ClO_2_. Moreover, a review [40] emphasized that it is a viable alternative to chlorhexidine. If the results are promising, further investigation of the interventions is needed for a more detailed and longer analysis. However, this detailed protocol will help improve studies in IOH research, and bring us one step closer to evidence-based treatment protocols.

## Strengths and limitations of the study

### Strengths

The efficacy of hyperpure chlorine dioxide has not been investigated in the therapy of intra-oral halitosis yet.Gas chromatography calibrated with a standardized gas mixture will be used to assess halitosis.This study can be the basis for more extended studies.

### Limitations

The long-term oral effects of hyperpure chlorine dioxide will not be monitored.First, 30 people each will be enrolled in two groups, then a sample size estimation will follow (lack of data on the intervention did not allow the sample size calculation). This will be a pilot study.

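### The reason given for having no sample size calculation is overstated: with the limit fixed at 1, 30 per arm could have been checked over a range of SDs, and any extension should rest on a blinded pooled SD

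*Protocol article*

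**What the plan says.** Under Sample size, the article calls the study exploratory because "the specific intervention has not yet revealed data in IOH in the literature". It then sets the first stage: "In the pilot phase, 30 participants each will be investigated in two groups". The next steps are "Then, the results of the primary outcome are used for sample size estimation" and "If the pilot can be continued, we will use it as an interim analysis in our study". Under Limitations it repeats the reason more strongly: "lack of data on the intervention did not allow the sample size calculation".

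The other inputs stand elsewhere in the article. Under Statistical methods: "we choose the non-inferiority limit (*d* = 1) as the most considerable clinically acceptable difference". Under Primary outcome, the endpoint is the change in a 0–5 organoleptic score, and two changes are named (baseline to immediately after rinsing, and baseline to 3 h). Withdrawal from study cites 10% dropout in previous studies. The Background cites studies of stabilised ClO2 mouthwashes and a meta-analysis, and the Discussion says "there is only one similar article [39] that compares chlorhexidine and ClO_2". Under Objectives, the hypothesis is one of non-inferiority. No SD, alpha, power or expected difference is stated.

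**The concern.** A non-inferiority sample size under an assumed true difference of zero needs the limit, the error rates and the SD of the outcome. It does not need an earlier effect estimate for the test product. The article fixes the limit but says that missing data on the product ruled out a calculation. The only empirical quantity missing was the SD of the score change, and the usual answer to an unknown SD is a table over a range.

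Two things are at stake. First, without the table nobody can see that 60 participants might already settle a question with a limit of 1. The article states a non-inferiority hypothesis and also calls the stage exploratory, so a reader cannot tell whether the 60-participant result is the test or a sizing step. Second, the extension is to be sized from the results of the primary outcome, with the pilot then reused as an interim analysis. As worded, this lets the decision to enrol more depend on the observed difference between the arms.

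**Working it through.** **Is there a figure to reproduce?** No. The article gives 30 per arm with no calculation behind it. The check asks what 30 per arm delivers at the stated limit.

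**Inputs from the article:** limit 1 (Statistical methods; no unit given, read as 1 scale point); 30 per arm (Sample size); 10% dropout (Withdrawal from study), so 30 × 0.9 = 27 per arm; two primary changes (Primary outcome).

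**Assumptions made here:** one-sided alpha 2.5%; true difference 0; power targets 80% and 90%; SD of change over a range, because none is given.

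**Power.** Normal approximation: power = Φ(1 / (SD × √(2/n)) − 1.96). At n = 30 and SD 1.0, √(2/30) = 0.2582, 1/0.2582 = 3.873, 3.873 − 1.96 = 1.913, and Φ(1.913) = 97.2%. The non-central t calculation with 58 degrees of freedom gives 96.8%. Results from the t calculation:

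| SD of change | Power, 30 per arm | n per arm for 80% | n per arm for 90% |
|---|---|---|---|
| 0.8 | 99.7% | 12 | 15 |
| 1.0 | 96.8% | 17 | 23 |
| 1.2 | 88.8% | 24 | 32 |
| 1.5 | 71.9% | 37 | 49 |

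**Largest SD at which the target power holds.** Normal approximation: SD_max = √(n/2) / (z_alpha + z_power). For n = 30 and 90% power, 3.873 / (1.960 + 1.282) = 1.195; for 80%, 3.873 / (1.960 + 0.842) = 1.382. The t calculation is slightly stricter:

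| Case | 90% power | 80% power |
|---|---|---|
| 30 per arm, alpha 2.5% | 1.175 | 1.359 |
| 27 per arm (10% dropout), alpha 2.5% | 1.112 | 1.287 |
| 30 per arm, alpha 1.25% (halved for two changes) | 1.075 | 1.229 |
| 27 per arm, alpha 1.25% | 1.018 | 1.163 |
| 30 per arm, alpha 2.5%, test product truly 0.25 point worse | 0.881 | 1.020 |
| 30 per arm, alpha 2.5%, test product truly 0.5 point worse | 0.587 | 0.680 |

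**Does the scale settle the SD?** No. Entry requires a score of at least 2 on a 0–5 scale. Without worsening, change runs from 0 to 5. Changes spread evenly over 0, 1, 2, 3 and 4 have SD √((5² − 1)/12) = 1.41, above every 90% limit in the table.

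**How precise is an SD from 60 participants?** Its relative standard error is about 1/√(2 × 59) = 9%, or about 0.11 at SD 1.17. If the true SD is 1.2, an estimate below 1.17 occurs about 42% of the time. A trigger that compares a bare point estimate with one threshold is therefore unreliable close to that threshold.

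**The case against.** The strongest defence is that variability data for this comparison really are missing, and that supplying them is a proper purpose of a pilot. The article declares the pilot openly and makes continuation conditional. Alpha, power and the expected difference are assumptions of this check. Assuming zero difference is also not neutral: it is where data on the hyperpure product would matter, since a true deficit of 0.25 point lowers the 90% limit to 0.88. Nor can it be checked whether the cited studies report an SD of organoleptic change at these time points. All of this stands. So does the point that a journal article may leave alpha and power to the full protocol or analysis plan; their absence is not the fault raised here.

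A reader might infer from the calculation that 30 per arm is already fully powered, that the pilot rests on a false premise, or that the first stage will be decisive in most plausible cases. The documents support none of these. Each would need an SD known to lie below the limits above, and the article gives none and its scale does not impose one. The unit of the limit is also unstated: if d = 1 were a standardised difference, 30 per arm would give 96.8% power whatever the SD, and the SD limits would not apply.

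What the defence does not rescue is the stated reason. An unknown SD calls for a range; it does not prevent a calculation.

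**Conclusion.** The concern holds in a limited form. Saying that no calculation was possible is too strong, because the article's own limit allows one over assumed SDs. At one-sided 2.5%, true difference 0 and a limit of 1 scale point, 30 evaluable per arm reaches 90% power up to SD 1.17 and 80% up to SD 1.36. These limits fall to 1.11 and 1.29 with 10% dropout, and to 1.02 and 1.16 if alpha is also halved for the two primary changes. Whether 30 per arm is adequate cannot be decided from the documents. The pilot design is legitimate; its stated justification, the unsettled status of the 60-participant stage and an extension sized from its primary results should be corrected.

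**What to change.** 1. In Sample size and Limitations, replace the statement that a calculation was not possible with the power table and its assumptions: unit of the limit, alpha, target power, SD range, dropout and handling of the two primary changes. If the limit changes, redo the table.
2. In Sample size, base any extension on the SD of change with both arms combined and unlabelled, and not on primary results by arm. Set a threshold that allows for dropout and the number of primary changes; under the assumptions above, with alpha halved, this is 1.02 for 90% power or 1.16 for 80%. Allow for the sampling error of the SD, for example by comparing an upper confidence limit with the threshold. An SD taken across both arms also contains one quarter of the squared difference between them; at a difference of 0.5 point this adds 0.0625 to the variance, so SD 1.0 becomes √1.0625 = 1.03, a small error on the cautious side.
3. State in advance that if no extension is triggered, the 60-participant stage is the non-inferiority test and is reported as such. If one is triggered, the test is done once, at the end.

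The cost is wording and a short table. The rule itself can call for more participants, but only where the SD requires them. The downside is less freedom to treat the first stage as purely exploratory.
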